**Table 1 Tab1:** **Schedule of events**

Assessment		Timeline (months post randomisation)		
	Baseline	8 weeks (+/- 7 days)	6 months (+/- 14 days)	12 months (+/- 14 days)
**Eligibility and consent**	X			
**Baseline data** (researcher/nurse completed from routinely collected data and ward staff)				
Rivermead Mobility Index (professional perspective on patient’s ability for stratification)	X			
Past medical history	X			
Lesion location and type (CT scan)	X			
Montreal Cognitive Assessment (MoCA)	X			
Randomisation (within 42 days post stroke)	X			
**Patient questionnaires** (completed via researcher interview with patient)				
Rivermead Mobility Index (patient’s perspective on ability)	X	X	X	X
ABILHAND scale	X^1^	X	X	X
Nottingham Extended Activities of Daily Living Scale	X^1^	X	X	X
General Health Questionnaire 12	X	X	X	X
EQ-5D	X	X	X	X
Barthel Index (postal version but collected face to face)	X	X	X	X
MSK-SSP Manikin	X^1^	X	X	X
Fatigue Assessment Scale		X	X	X
Health Economics Resource Use Questionnaire	X	X	X	X
**Carer questionnaires** (Carer completed)				
Caregiver Burden Scale		X	X	X
EQ-5D	X	X	X	X
Health Economics Resource Use Questionnaire	X^1^	X	X	X
**Qualitative follow-up**				
Patient/therapist perspective regarding use of IMP		X		
**Clinical follow-up data** (researcher/therapist/nurse completed)				
Treatment data (rehabilitation and drug compliance)		X		
Modified Rankin Scale		X	X	
Montreal Cognitive Assessment (MOCA)		X	X	X
Serious and non-serious adverse event monitoring	Continuous reporting as occur			
New significant medical/surgical illness (e.g. for stroke, myocardial infarction, cancer, fracture, elective surgical procedures)			X	X

^1^Pre stroke.

#### Sample size

We plan to recruit 572 patients from more than 50 hospitals across the UK. This will provide 90% power at 5% significance to detect 50% relative difference between the placebo and active treatment group in the proportion walking independently at eight weeks post randomisation (as measured by the RMI score 7 or greater and who also answer ‘yes’ to item number 7). This assumes the same control rate of 26% as in the Scheidtmann study
[9] and will ensure the minimum improvement that can be detected is 39% of patients on active treatment who are walking independently by eight weeks.

The primary intention to treat (ITT) analysis will include all randomised patients as it will assume that patients who die or are lost to follow-up are unable to walk independently.

This sample size also provides 80% power to detect a small to moderate effect size of 0.3 in key secondary outcomes (for example, ABILHAND - to measure functional upper limb activities; the NEADL scale measuring instrumental activities of daily living, such as outdoor mobility and household tasks). It is important that the study has sufficient power to detect real change in these secondary outcomes given that they are (1) important functional parameters in addition to walking and (2) are also likely to change if the treatment is effective. For all secondary analyses, loss to follow up has been estimated at 10% at eight weeks (of those surviving stroke at two weeks), rising to 20% by twelve months.

#### Analysis

Statistical analysis is the responsibility of the CTRU statistician and a final statistical analysis plan will be written before any analysis is undertaken. All analyses will be conducted on the ITT population defined as all participants randomised regardless of non-compliance with the intervention. An overall two-sided 5% significance level will be used for all endpoint comparisons.

Primary analysis of independent walking ability at eight weeks post-randomisation (defined by a score of 7 or above and who also answer ‘yes’ to item 7 on the RMI) will be undertaken using logistic regression, while adjusting for gender, type of stroke, centre and RMI at baseline. For the primary outcome ITT analysis, it will be assumed that patients who die or are lost to follow-up are categorised as ‘unable to walk independently’. A sensitivity analysis will be undertaken to test the robustness of conclusions to this assumption. RMI will be analysed as a continuous measure as part of secondary analyses.

Other outcome measures will be analysed for each time point by regression models appropriate to the data type. Such analyses will adjust for patient-level covariates included as strata within the randomisation process including gender, type of stroke, centre and RMI. Appropriate methods will be used to handle missing data.

Potential predictors (fatigue, depression, pain, medical and surgical events, cognitive function, activities of daily living, number of rehabilitation therapy sessions and number of tablets taken) of response to Co-careldopa will be explored using baseline measurements taken for primary and secondary outcomes. In addition, we plan to model the relationship between potential moderator and mediator variables and treatment effect.

A per-protocol analysis will be carried out to indicate whether results are sensitive to the exclusion of patients who violated the protocol.

The number of patients reporting a SAE (up to 30 days after the last dose of treatment) and details of all SAEs will be reported for each treatment group.

The Trial Statistician will be blinded to treatment group allocation throughout the trial until the database has been downloaded for final analysis. Only the Safety Statistician, Supervising Trial Statistician, back-up Safety Statistician and Safety Data Manager will have access to unblinded treatment group allocation prior to final analysis.

The primary within-trial economic analysis will be a cost-utility analysis yielding cost per incremental quality-adjusted life year (QALY). A secondary within-trial analysis will estimate the incremental cost per patient achieving independent walking (as determined by a score of ≥7 on the RMI) at eight weeks post-randomisation for Co-careldopa versus placebo. A decision-analytic model will be developed to estimate the lifetime costs and effects (QALYs) of the interventions and the resulting incremental cost-effectiveness ratio (ICER) referenced to the NHS willingness to pay per QALY gain threshold. Extensive deterministic and probabilistic sensitivity analyses will be conducted to estimate the level of uncertainty around the results. QALY values will be based on EQ-5D utility and the perspective of the analysis will be Health and Personal Social Care.

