#### Inclusion criteria

New or recurrent clinically diagnosed ischaemic or haemorrhagic (excluding subarachnoid haemorrhage) stroke within 5 to 42 days prior to randomisation.Cannot walk 10 metres or more indoors independently (that is, without use of physical assistance)Rivermead Mobility Index score of <7.Expected to need rehabilitation treatmentAged 18 years or aboveAble to give informed consentAble to access continuity of rehabilitation treatment following discharge from hospital which is available within five days following hospital discharge.Expected to be able to comply with the treatment schedule (for example, swallow whole tablets)Expected to be in hospital for at least the first two doses of trial medication

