**Patient recruitment pathway.**

Informed written consent will be obtained from all participants and will also be sought from carers (if present) to allow information relating to carer burden to be collected.

Participants who fulfil the eligibility criteria will be randomised on a 1:1 basis to receive either Co-careldopa or placebo. Stratified randomisation will be used to ensure that treatment groups are well-balanced for: (1) recruiting centre; (2) type of stroke (primary intracranial haemorrhage; infarct); and (3) RMI score 0–3; >3 but <7.

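### The stated covariates for the secondary models wrongly count gender as a randomisation stratum and omit the outcome's own baseline where the schedule collects it

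*Protocol article*

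**What the plan says.** The Analysis section of the protocol article states the rule for outcomes other than the primary: "Such analyses will adjust for patient-level covariates included as strata within the randomisation process including gender, type of stroke, centre and RMI". The primary logistic model uses the same four variables, "adjusting for gender, type of stroke, centre and RMI at baseline", but there gender is not called a stratum.

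The randomisation text under Recruitment and randomisation gives the strata as "1) recruiting centre; (2) type of stroke (primary intracranial haemorrhage; infarct); and (3) RMI score 0–3; >3 but <7". Gender does not appear.

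Table 1 (Schedule of events) shows which starting values exist. Barthel, entered as "Barthel Index (postal version but collected face to face"), and GHQ-12 are taken at baseline and at every follow-up. ABILHAND and NEADL have a baseline entry footnoted as pre-stroke. RMI has two baseline entries: a professional rating used for stratification, and "Rivermead Mobility Index (patient’s perspective on ability"), which alone is repeated at follow-up. Modified Rankin, the Fatigue Assessment Scale and the Caregiver Burden Scale have no baseline entry.

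**The concern.** The Analysis and randomisation sections disagree about what the strata are. Whoever writes the analysis code cannot tell whether gender was balanced by design or is simply a chosen covariate.

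The rule also ties adjustment to the strata. The list is introduced as open, but open only to other strata, and RMI is the only outcome measure among them. Read as written, baseline Barthel does not enter the Barthel model and baseline GHQ-12 does not enter the GHQ-12 model. An outcome's own starting value is often its best single predictor. Leaving it out gives wider confidence intervals than the collected data allow, and leaves chance imbalance in that value in the estimate. The Sample size section stresses adequate power for the secondary outcomes, so the stated rule works against the trial's own aim.

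**Working it through.** **Step 1. Strata.** The randomisation section names centre, stroke type and RMI band. The Analysis section names gender, stroke type, centre and RMI. The only difference is gender.

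**Step 2. Which starting values could be added.**

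| Secondary outcome | Baseline entry in Table 1 | In its own model as stated |
|---|---|---|
| Barthel | post-stroke | no |
| GHQ-12 | post-stroke | no |
| ABILHAND | pre-stroke only | no |
| NEADL | pre-stroke only | no |
| RMI (continuous) | post-stroke, two raters | yes, rater and form not stated |
| Modified Rankin | none | not possible |
| Caregiver Burden Scale | none | not possible |

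**Step 3. The plan's own secondary power figure.** Inputs from Sample size: 572 patients, effect size 0.3, stated power 80%, loss 10% at eight weeks and 20% by twelve months. Inputs from elsewhere: 1:1 allocation, and "An overall two-sided 5% significance level will be used for all endpoint comparisons". I take the losses as fractions of 572.

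Power = Φ(0.3 × √(n/2) − 1.96), with n per arm:
- no loss, n = 286: 94.8%
- 10% loss, n = 572 × 0.9 / 2 = 257.4: 92.6%
- 20% loss, n = 572 × 0.8 / 2 = 228.8: 89.4%

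The stated 80% is therefore not reproduced; the planned size gives more. For 80% power, n = 2 × (1.96 + 0.842)² / 0.3², about 175 per arm or 350 in total. Allowing for loss, that is 350 / 0.9 = 389 or 350 / 0.8 = 438, both below 572.

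**Step 4. Effect of adding the outcome's own baseline.** Let r be the partial correlation of that baseline with the outcome, given the covariates already in the model. Residual variance is multiplied by 1 − r² and the standard error by √(1 − r²), so

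Power = Φ(0.3 / √(1 − r²) × √(n/2) − 1.96).

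The documents give no value for r, so a range is shown.

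| Assumed r | Residual variance factor | Standard error factor | Power at 8 weeks (n = 257.4) | Power at 12 months (n = 228.8) | Effect detectable with 80% power at 12 months |
|---|---|---|---|---|---|
| 0 | 1.00 | 1.00 | 92.6% | 89.4% | 0.262 |
| 0.3 | 0.91 | 0.95 | 94.6% | 92.0% | 0.250 |
| 0.5 | 0.75 | 0.87 | 97.6% | 96.0% | 0.227 |
| 0.7 | 0.51 | 0.71 | 99.8% | 99.4% | 0.187 |

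For r = 0.5 at twelve months: √0.75 = 0.866 and √114.4 = 10.70, so 0.3 / 0.866 × 10.70 − 1.96 = 1.75 and Φ(1.75) = 96.0%.

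The r = 0 row takes the standard deviation as 1 after the planned covariates. Because r is partial, baseline RMI may already carry part of what baseline Barthel would add, which pushes r downwards.

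**The case against.** The strongest reply is that a final statistical analysis plan is promised before any analysis, and that covariate lists and coding normally belong there. That holds for detail such as which RMI rating enters the primary model. It does not dispose of the point, because the article states a covariate rule rather than leaving it open. A later plan that follows that rule would carry over both the error about gender and the omission.

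A second reply is that the analysis is valid as it stands. This is correct. Under randomisation, omitting a prognostic covariate does not bias the comparison on average. Gender is in the model whether or not it was a stratum.

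Three stronger readings are tempting, and the documents do not support them.
- A reader might infer that every secondary model ignores a recorded baseline. RMI is already in the models, ABILHAND and NEADL have only pre-stroke values, and Modified Rankin, the Fatigue Assessment Scale and the Caregiver Burden Scale have none. EQ-5D has a baseline but is listed under health economics.
- A reader might infer that leaving out age and days since stroke is an error. The inclusion criteria set "stroke within 5 to 42 days prior to randomisation" and an age limit, so both should be derivable, but Table 1 lists neither as a data item. Adding them is an option.
- A reader might infer that the primary analysis loses material power. Its model already adjusts for four covariates including baseline RMI, and the documents give nothing from which a further gain could be calculated.

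**Conclusion.** The point holds in a limited form. The statement that gender is a stratum contradicts the randomisation section and must be reconciled. The stated secondary covariate set also omits collected starting values: clearly for Barthel and GHQ-12, and with less promise for ABILHAND and NEADL, where a pre-stroke score may predict post-stroke function only weakly.

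The loss is one of precision. At twelve months it ranges from under 3 percentage points of power at r = 0.3 (89.4% to 92.0%) to 10 points at r = 0.7 (89.4% to 99.4%). These figures rest on assumed partial correlations, a linear model, and 20% loss taken from 572. No power shortfall is being repaired, since 89.4% already exceeds the stated 80%. It is a worthwhile improvement at little cost, not a threat to the trial's conclusions.

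**What to change.** - Add each secondary outcome's own baseline value to its model where Table 1 collects one: the post-stroke score for Barthel and GHQ-12, the pre-stroke score for ABILHAND and NEADL.
- For the continuous RMI outcome, use the patient-rated baseline score as a continuous covariate, because that version is repeated at follow-up.
- Keep the true strata (centre, stroke type and RMI) in the models.
- Describe gender as an additional prognostic covariate, or otherwise reconcile the Analysis and randomisation sections.
- Age and days since stroke may be added if the data are held and they are prespecified.

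The cost is wording in the analysis plan. The outcome baselines are already scheduled, so no new assessment is needed. The plan should say how a missing baseline value is handled, so that adjustment does not remove randomised patients. The change should be fixed before unblinding, because covariates added later can look data-driven.

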Secondary objectives are to determine: (1) the impact on physical functioning and mood at eight weeks, six months and twelve months; (2) potential moderators and mediators of effect at eight weeks, six months and twelve months; (3) implementation within routine healthcare services; and (4) the cost-effectiveness of co-careldopa augmented rehabilitation for stroke compared to usual care within stroke services.Investigation of impact on physical functioning and mood at eight weeks, six months and twelve months To compare the proportion of patients who are walking at six and twelve months post-randomisation between the groups (as measured by a score of 7 or higher on the RMI and who also answer yes on item number 7)To compare activities of daily living, mobility and dependency using the RMI (continuous), Barthel Index, Modified Rankin Scale, Nottingham Extended Activities of Daily Living (NEADL) scale and ABILHAND between groups.To compare psychological distress/mood between groups using the General Health Questionnaire 12 (GHQ-12)To compare carer burden between groups using the Caregiver Burden Scale (CBS)Investigate potential moderators and mediators of effect at eight weeks, six months and twelve months To investigate whether baseline patient clinical characteristics and investigations (for example, routine brain CT scanning) help to predict those who might benefit from Co-careldopa augmented rehabilitationTo investigate whether key factors (for example, fatigue measured by the Fatigue Assessment Scale (FAS)), concurrent musculoskeletal symptoms, signs and pain (using the MSK SSP manikin) and cognitive function (using the Montreal Cognitive Assessment (MoCA)) influence the short and long term effect of Co-careldopa on physical functioningInvestigation of implementation within NHS To assess the adverse event profile associated with Co-careldopa in addition to conventional NHS stroke rehabilitation treatmentTo investigate the practical implications of delivering this combined intervention within routine NHS acute and early community care of people with strokeTo assess the acceptability of Co-careldopa treatment to stroke patients (study drug adherence will be measured)To determine the cost-effectiveness of Co-careldopa versus placebo for rehabilitation after stroke

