#### Intervention

Patients will take a single oral tablet 45 to 60 minutes before routine NHS physical or occupational therapy sessions for a maximum of six weeks. Routine physical or occupational therapy is defined as active physical treatment (that is, most physical and occupational therapy directed at motor skills, such as walking, transfers, and dressing but not solely psychological input sessions or speech and language therapy). This also includes programmed rehabilitation delivered by rehabilitation assistants.

The dose and timing of the medication reflects current evidence on use of Co-careldopa in this context (9, 11, 12, 13). As part of this trial a pragmatic approach will be taken. Although the dose should be taken optimally between 45 to 60 minutes prior to the rehabilitation treatment session it is recognised that there may be occasions where, for example, the therapist is unable to contact the patient to remind them to take the tablet or the patient may forget. It is acceptable for the tablet to be taken within 0 to 15 minutes before the start of therapy in these situations. The peak effect of Co-careldopa is 0.5 to 2 hours after an oral dose. If the patient is scheduled to have two therapy sessions directly one after the other or within three hours of a dose then a repeat dose is not given before the second of the therapy sessions. If the patient is having more than two physical or occupational therapy sessions, the dose will not be administered more than twice during any one 24 hour period.

Assuming a maximum of two sessions of physiotherapy (PT) or occupational therapy (OT) per day for 30 days over a six week treatment period, each patient will receive a maximum of 60 tablets during their participation in the intervention phase of the trial. Investigational Medicinal Product (IMP) with usual NHS rehabilitation treatments will be continued for a maximum of six weeks as long as it is deemed that the patient would benefit from ongoing rehabilitation. The duration of treatment may be less if the patient is clinically deemed not to require further rehabilitation treatment. The decision about need for rehabilitation interventions (when to start, finish and type) will be made by the treating clinicians, therapists and nurses in consultation with patients and families as part of the routine management of the patient (refer to Figure 

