#### Outcomes

The primary outcome will assess whether patients can walk independently at eight weeks post-randomisation as measured by a RMI score of 7 or higher and can walk 10 metres with an aid if necessary but with no standby help (that is, answer ‘yes’ to item number 7 on the RMI).

Secondary patient outcomes (all measured at eight weeks, six and twelve months):

*Physical functioning:* RMI (continuous), Barthel Index (dependency measure), Modified Rankin Scale, NEADL scale (extended activities of daily living), ABILHAND (bilateral arm activities)*Mood:* GHQ-12*Potential moderators and mediators of treatment effect*: baseline clinical characteristics and investigations (for example, routine brain neuroimaging) will be collected to predict those who might benefit from Co-careldopa augmented rehabilitation; fatigue (FAS)), concurrent musculoskeletal symptoms, signs and pain (using the MSK SSP manikin) and cognitive function (using the MoCA).*Implementation within NHS*: to investigate the practical implications of delivering this intervention within routine NHS acute and early community care of people with stroke; and to assess acceptability of Co-careldopa treatment to stroke patients through measuring study drug adherence will be undertaken with participants at the week 8 assessment.

Process outcomes: Standardised therapy forms will be used to document the type of rehabilitation received by the trial participant. These logs will also capture information ease of compliance with timing of treatment schedule, IMP packaging, clarity of instructions and labelling.

Carer outcomes*:* The CBS will be administered at eight weeks, six and twelve months to assess carer outcomes.

Safety: Adverse events, whether volunteered by the patient or carer, or identified by the therapist or researcher, until the eight week follow up appointment are documented. As an inpatient, the local research team will monitor the patient for the occurrence of adverse events. Following discharge from hospital, detection of most adverse events will occur through spontaneous reporting by patients, their carers, attending therapists or via the scheduled visits by the researcher. Serious adverse events (SAEs) will be reported to the CTRU up to 30 days after the last dose of protocol treatment. All serious unexpected suspected adverse reactions (SUSARs) are reported to the CTRU within 24 hours and expedited reported to the MHRA, ethics committee and Sponsor where applicable.

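### The only stated SAE summary ends 30 days after each patient's last dose, so the observation window varies with recovery; a count over a fixed period from randomisation should be added

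*Protocol article*

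**What the plan says.** All references are to the protocol article.

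- **Analysis.** The SAE summary is "The number of patients reporting a SAE (up to 30 days after the last dose of treatment". On presentation, the section says only that "details of all SAEs will be reported for each treatment group". No other SAE summary window is stated, nor any SAE test, rate per person-time or exposure adjustment. The same section says that every analysis uses the ITT population, meaning all randomised participants whatever their compliance.
- **Outcomes, Safety paragraph.** Two clocks appear. Adverse events "until the eight week follow up appointment are documented". Separately, "Serious adverse events (SAEs) will be reported to the CTRU up to 30 days after the last dose of protocol treatment".
- **Table 1.** One row, "Serious and non-serious adverse event monitoring", is marked as continuous reporting and has no end date.
- **Intervention.** Trial medication with rehabilitation "will be continued for a maximum of six weeks as long as it is deemed that the patient would benefit from ongoing rehabilitation". Also: "The duration of treatment may be less if the patient is clinically deemed not to require further rehabilitation treatment".
- **Objectives.** One secondary aim is "To assess the adverse event profile associated with Co-careldopa".

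**The concern.** The end of the SAE window is tied to the last dose. Doses are given only before therapy sessions, so the last dose tracks the last qualifying session, and that depends partly on how well the patient has recovered. Recovery is what the drug is meant to change: the Sample size section hopes for 39% walking independently on active treatment against 26% on placebo. If active patients need less rehabilitation and stop sooner, they are observed for fewer days, and fewer of them can be counted with an SAE even when the daily risk is the same in both arms. A real excess of SAEs on the drug would be diluted in the same way.

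There is also a gap in definition. A randomised patient who never takes a dose has no last dose and so no window, although the article puts every randomised patient in every analysis.

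At stake is whether the by-arm SAE counts, which readers will set side by side, can be read as a randomised contrast.

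**Working it through.** **The plan's own figure.** There is none for this point. The article gives no SAE rate and no early-stopping rate, and its sample size of 572 concerns walking. All rates below are assumptions. Days are counted from randomisation, taking the first dose as close to it.

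**Step 1: window length.** Window = day of last dose + 30. The cap of six weeks is day 42.

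| Last dose | Window | Share of longest window |
|---|---|---|
| Day 42 | 72 days | 100% |
| Day 26 | 56 days | 78% |
| Day 21 | 51 days | 71% |
| Day 14 | 44 days | 61% |
| Day 7 | 37 days | 51% |

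The eight-week visit is nominally day 56. A last dose before day 26 closes the SAE window before that visit; a last dose after day 26 leaves it open beyond the visit. So the two clocks in the Safety paragraph cross.

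**Step 2: effect on the counts with no true drug effect.** Let r be the 72-day SAE risk under full treatment and h the constant daily hazard, so h = −ln(1 − r)/72. Let a fraction f of an arm stop on day s and the rest on day 42. Then

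arm risk = f × [1 − exp(−h(s + 30))] + (1 − f) × r.

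Worked example: r = 15%, s = day 14, f = 10% on placebo and 30% on active.

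- Risk in an early stopper: 1 − 0.85^(44/72) = 0.0945.
- Placebo: 0.10 × 0.0945 + 0.90 × 0.15 = 0.1445.
- Active: 0.30 × 0.0945 + 0.70 × 0.15 = 0.1334.
- Apparent risk ratio: 0.1334/0.1445 = 0.92, a difference of −1.1 percentage points.

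Results for r of 10%, 15%, 20% and 30% and s of day 14 or 21:

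| Stopping early, placebo vs active | Apparent risk ratio |
|---|---|
| 10% vs 20% | 0.96 to 0.97 |
| 10% vs 30% | 0.92 to 0.95 |
| 26% vs 39% (every independent walker stops early) | 0.95 to 0.96 |

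In the 10% vs 30% row the risk difference runs from −0.6 to −2.1 points. If f and s are the same in both arms, the two risks are identical and the ratio is 1.00.

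**Step 3: masking of a true harm.** With a true hazard ratio of 1.25, r = 15%, and 10% vs 30% stopping on day 14, the observed risk ratio is 1.13. Over a fixed 56 days it would be 1.23.

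**Step 4: the fixed window.** With equal hazards, a common 56-day period gives a ratio of 1.00 whatever the stopping pattern.

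**The case against.** The strongest reply is that this is a descriptive safety report using a familiar convention. Thirty days after last dose is a common treatment-emergent limit, and it is generous for a drug whose plasma half-life the Background gives as 1 to 3 hours. The article is condensed and says that a final SAP will be written; an extra table could be specified there. The DMEC also reviews unblinded adverse event data quarterly. This stands as a reason to keep the last-dose count. It does not remove the point, because the article fixes a window, and that window is the only one stated for SAEs.

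Some stronger readings are tempting but not supported:

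- *That the arms are formally compared on SAEs.* The text promises a report by group and states no SAE test.
- *That the result is biased.* This needs stopping to differ between arms, or to be related to treatment. The article gives no data on either.
- *That intolerance shortens observation.* The Intervention section names only the lack of further need for rehabilitation. Stopping for side effects is a plausible inference, but it is not in the text. A patient who stops because of an SAE is already counted.
- *That serious events after the window are lost.* The eight-week documentation rule speaks of adverse events without limiting them to non-serious ones, and Table 1 lists both kinds together. Serious events up to about day 56 may well be on record for early stoppers. Table 1 also collects new significant illness at 6 and 12 months.
- *That the deficit could be a fifth or more.* A mean treatment of 28 vs 42 days gives 58/72 = 0.81, and 21 vs 42 days gives 51/72 = 0.71. But 42 days is the cap, so a placebo mean of 42 means that no placebo patient stops early. Qualifying therapy also covers transfers and dressing, so regaining walking need not end treatment.

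**Conclusion.** The point holds in a limited form. The one SAE summary stated has a window whose length depends on a post-randomisation event linked to recovery, and it has no meaning for a patient who takes no dose. The by-arm counts are like for like only if stopping is equal across arms and unrelated to treatment.

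The likely distortion is modest: an apparent risk ratio of about 0.92 to 0.97 under no true effect, for the assumed 72-day SAE risks of 10% to 30%, last doses on day 14 or 21 in early stoppers, a constant hazard, and 10 to 20 percentage points more early stopping on active treatment. Its direction would favour the drug if active patients stop sooner. This does not show that the safety results will be biased. It is a weakness in a stated rule that is easy to repair.

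**What to change.** 1. In the Analysis section, make the main by-arm SAE summary the number of patients with at least one SAE from randomisation to the eight-week visit, for all randomised participants, whether or not they took or completed trial medication.
2. Keep the count to 30 days after last dose as a secondary, treatment-emergent summary.
3. Reconcile the two collection rules in the Safety paragraph of Outcomes with the open-ended row in Table 1. State explicitly that serious events are recorded to at least eight weeks for everyone, including those who stop early.

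Cost: wording and one extra table. If the eight-week documentation already includes serious events, as the text suggests, no new data are needed; the sponsor should confirm this. The main summary is shorter for treatment completers, about 56 days instead of 72, but their later events stay in the secondary count. The eight-week visit may vary by 7 days either way under Table 1, but that tolerance is set by the visit schedule and does not depend on the last dose.

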## Methods/design

### Objectives

The primary objective relates to physical functioning and will compare the proportion of patients between treatment groups who are walking independently at eight weeks post-randomisation (as measured by a score of 7 or higher and who also answer ‘yes’ to item number 7 on the RMI).

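### The secondary cost-per-walker analysis defines independent walking as RMI of 7 or more alone, whereas every other definition in the protocol also requires a yes on item 7

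*Protocol article*

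**What the plan says.** The Protocol article defines independent walking in six places.

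- Objectives, primary: "as measured by a score of 7 or higher and who also answer ‘yes’ to item number 7 on the RMI".
- Objectives, walking at six and twelve months: "as measured by a score of 7 or higher on the RMI and who also answer yes on item number 7".
- Outcomes, primary: "measured by a RMI score of 7 or higher and can walk 10 metres with an aid if necessary but with no standby help", which the text equates with a yes on item 7.
- Sample size: "as measured by the RMI score 7 or greater and who also answer ‘yes’ to item number 7".
- Analysis, primary: "defined by a score of 7 or above and who also answer ‘yes’ to item 7 on the RMI".
- Analysis, economic paragraph, secondary within-trial ratio: "achieving independent walking (as determined by a score of ≥7 on the RMI) at eight weeks post-randomisation".

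The first five have two parts. The sixth has one. It gives no reason for the difference and does not refer back to the primary outcome. The same paragraph makes cost per QALY the primary economic analysis and adds a lifetime model, also in QALYs valued with EQ-5D.

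**The concern.** The label and the eight-week time point are those of the primary outcome, but the rule is looser. The two rules disagree on one kind of patient: RMI total of 7 or more with a no on item 7. That patient is a success in the cost-per-walker ratio and a failure in the clinical result.

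A cost per additional independent walker is useful to a reader only if its denominator can be traced to the trial's walking effect. If the two rules produce different counts, one report would give two success rates under one name. Leaving both rules in the text also leaves open which one the economic analysis follows, and that should be settled before allocation is revealed.

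**Working it through.** **1. Which definition the design rests on.** Inputs from Sample size, Analysis and the randomisation text: 26% versus 39%, 90% power, two-sided 5%, 1:1 allocation, no inflation for losses.

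- Uncorrected n per arm = [1.960·√(2·0.325·0.675) + 1.2816·√(0.26·0.74 + 0.39·0.61)]² / 0.13² = 270.7, so 271 (542 in total).
- With continuity correction: (270.7/4)·[1 + √(1 + 4/(270.7·0.13))]² = 285.9, so 286 per arm, 572 in total.

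This matches the stated 572. The Sample size section ties these rates to the two-part definition, so the design-stage effect for that definition is 39 − 26 = 13 points, or 0.13·286 ≈ 37 extra independent walkers.

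**2. Direction.** Everyone who meets the two-part rule also meets the score-only rule. In each arm, score-only count = two-part count + number with a total of 7 or more and a no on item 7. The economic count cannot be smaller than the primary count.

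**3. Size.** The documents do not give the size of the discordant group, so every figure below is an assumption added to 26%/39%. Incremental cost is held fixed, so the ratio is multiplied by 13 divided by the new difference.

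*(a) Discordant patients as an equal absolute share of each arm*

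| Added points, control/active | Rates | Counts of 286 | Difference | Ratio × |
|---|---|---|---|---|
| 0/0 | 26% / 39% | 74 / 112 | 13 | 1.00 |
| 2/2 | 28% / 41% | 80 / 117 | 13 | 1.00 |
| 5/5 | 31% / 44% | 89 / 126 | 13 | 1.00 |

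*(b) Discordant patients as an equal proportion of those scoring 7 or more*

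- 5%: 26/0.95 = 27.4%, 39/0.95 = 41.1%; difference 13/0.95 = 13.7 points; ratio × 0.95.
- 10%: 26/0.90 = 28.9%, 39/0.90 = 43.3%; difference 13/0.90 = 14.4 points; ratio × 0.90.

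*(c) Unequal absolute shares*

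| Added points, control/active | Difference | Ratio × |
|---|---|---|
| 2/5 | 16 | 0.81 |
| 5/2 | 10 | 1.30 |
| 0/5 | 18 | 0.72 |
| 5/0 | 8 | 1.63 |

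Cases (a) and (b) do not conflict. In (a) the share is of all patients in the arm; in (b) it is of those scoring 7 or more, so the arm with more such patients gains more.

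**4. Scale against sampling error.** At 26% and 39% with 286 per arm, the standard error of the difference is √[(0.1924 + 0.2379)/286] = 3.9 points, a 95% half-width of about 7.6. The shift in (b), 0.7 to 1.4 points, is small beside that.

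**The case against.** The best defence is that the economic sentence is shorthand. It borrows the primary outcome's name and time point, sits in a parenthesis, comes after five statements of the full definition, and announces no separate endpoint. In a condensed article that is quite possible, and the full economic plan is not shown. This lowers the likelihood that the analysts intend a second endpoint. It does not remove the contradiction, because the sentence does not leave the measure undefined: it states a criterion, and that criterion differs from the others.

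A second defence is that a total of 7 or more may in practice nearly always come with a yes on item 7, so that nothing changes. The documents cannot exclude this. They do, however, treat the score and the walking test as separate conditions: the outcome definition joins them with an and, and the inclusion criteria list inability to walk 10 metres and RMI below 7 as two items.

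Some stronger readings are tempting but unsupported:

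- A reader might infer that the looser rule counts non-walkers as walkers. Item 7 requires that the patient "can walk 10 metres with an aid if necessary but with no standby help". Someone who fails it may still walk with standby help, and someone using an aid can pass.
- A reader might infer that the treatment difference must change. Case (a) shows that it need not.
- A reader might infer that deaths and losses are handled differently in this ratio. The economic paragraph states no different handling, so there is no contradiction there to correct.

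**Conclusion.** The inconsistency is real and explicit, and its scope is narrow. It affects one secondary within-trial ratio. A reader might take it to undermine the economic evaluation as a whole; it does not, because the primary cost-per-QALY analysis and the lifetime model do not use the walking definition. The primary clinical analysis and the 572 are unaffected.

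The direction for the counts is certain: the score-only rule gives the same number of successes or more in each arm. The effect on the ratio is unknown and may be nil. It is nil if the discordant group is the same absolute share of each arm. The difference is 13.7 to 14.4 points instead of 13.0 if 5–10% of those scoring 7 or more fail item 7 in both arms. The ratio can move in either direction if the absolute shares differ. All of these figures assume the design rates and a fixed incremental cost. The point deserves correction because the definition should be fixed before analysis, not because a large distortion has been shown.

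**What to change.** In the economic paragraph of the Analysis section, and in any economic analysis plan, define the effect in this ratio as the primary outcome: RMI total of 7 or more and a yes on item 7 at eight weeks. A cross-reference to the primary outcome would be enough. If a score-only version is wanted, label it as a separate sensitivity analysis and give its rationale. The cost is one line of text. Item 7 is already collected for the primary outcome, so no new data are needed, and neither sample size nor significance level changes.
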